# Synopsis (according to GCP-V § 7 (3) Nr. 19 in German language)

| **Titel der Studie** | Kunsttherapie zur Symptomreduktion bei akuter Schizophrenie  – eine randomisierte kontrollierte Pilotstudie |
| --- | --- |
| **Art des Vorhabens** | Monozentrische, einfach-verblindete, randomisiert-kontrollierte Pilotstudie |
| **Leiter der klinischen Prüfung/**  **Hauptprüfer** | [name]. phil. [name]  Kunsttherapie Berlin  Kunsthochschule Berlin-Weißensee  [name]  [contact]  Dr. med. [name]  Psychiatrische Universitätsklinik der Charité im St. Hedwig-  Krankenhaus  [name]  [contact]  [contact]  [contact]  Dr. med. [name]  Psychiatrische Universitätsklinik der Charité im St. Hedwig-  Krankenhaus  [name]  [contact]  [contact]  [contact] |
| **Prüfzentren** | Charité Universitätsmedizin Berlin,  Klinik für Psychiatrie und Psychotherapie, Campus Mitte,  Psychiatrische Universitätsklinik der Charité im St. Hedwig-  Krankenhaus |
| **Hypothese** | **Haupthypothese:** Die kunsttherapeutische Intervention führt im  Vergleich zu einer Kontrollbedingung zu einer schnelleren und  nachhaltigeren Symptomreduktion.  **Nebenhypothesen:**  NH1: Kunsttherapie führt zu einer größeren Zufriedenheit der  Patienten mit der Behandlung  NH2: Kunsttherapie ist assoziiert mit höherer Lebensqualität.  NH3: Kunsttherapie ist verbunden mit einer Zunahme der  Selbstwirksamkeitserwartung.  NH4: Kunsttherapie ist assoziiert mit einer Verbesserung von  Mentalisierungsfunktionen wie der ToM und der Erkennung von  Emotionen in sozialen Situationen |
| **Fragestellung aufbauend auf wissenschaftlichem Hintergrund** | Ist Kunsttherapie zur Behandlung von stationär geführten  Patienten in der akuten/ subakuten Phase einer schizophrenen  Erkrankung wirksam im Vergleich zur Standardbehandlung  (treatment as usual, TAU)?   - In der stationären Behandlung exazerbierter oder ersterkrankter schizophrener Patienten sind neben der antipsychotischen psychopharmakologischen Therapie und supportiven ärztlich-psychotherapeutischen Behandlung weitere gezielte therapeutische Interventionen notwendig, um den Genesungsprozess zu fördern. Die meisten Kliniken bieten dafür ein therapeutisches Programm mit verschiedenen Verfahren wie z.B. Psychotherapie, Psychoedukation, Ergotherapie, Bewegungstherapie, Musiktherapie, Dramatherapie und Kunsttherapie an. Dabei ist die gesicherte Evidenz über die Wirksamkeit der unterschiedlichen Interventionen sehr gering. In dieser Studie soll die Wirksamkeit der Kunsttherapie, einer seit über 60 Jahren etablierten Behandlungsform, bei Patienten mit akuten schizophrenen Psychosen geprüft werden. - Bei Patienten, die unter desorganisiertem Denken, Wahn, Sinnestäuschungen, Ich-Störungen, affektiven und/oder psychomotorischen Symptomen leiden und dadurch in ihrer Lebensqualität, Leistungsfähigkeit und sozialen Interaktion stark beeinträchtigt sind, ist der Aufbau eines stabilen therapeutischen Bündnisses und eine Symptomreduktion mithilfe antipsychotischer Arzneimittel die Behandlungsmethode der Wahl. Dafür ist häufig ein stationärer Rahmen notwendig. - In den sechziger Jahren wurden in den USA und Großbritannien Studien zur Kunsttherapie bei Menschen mit psychischen Störungen durchgeführt, die den Prozess der Therapie untersuchten und die Behandlungsform entwickelten. Die Kunsttherapie wurde als Studienfach an internationalen und seit ca. 20 Jahren an deutschen Hochschulen etabliert. Von Beginn an wurden auch an Schizophrenie leidende Menschen mit Kunsttherapie behandelt. Erkenntnisse über die positive Auswirkung von praktizierter künstlerischer Aktivität bei schizophrenen Patienten, wobei es zu einer Reduktion subjektiven Leidens durch den Ausdruck von Gefühlen und neuer Einsichtsmöglichkeiten im Kunstwerk kommt, gehen bis ins neunzehnte Jahrhundert zurück. - In einem Cochrane-Review von 2005 haben Ruddy et al. [4] die Evidenz für die Behandlung schizophrener Patienten mit Kunsttherapie zusammengefasst. Dabei wurden Hinweise für die Wirksamkeit dieser Therapieform in zwei in eine Metaanalyse eingeschlossenen Studien [5; 6] beschrieben. Randomisierte kontrollierte Studien, die eine gut abgesicherte Aussage über die Wirksamkeit und Unbedenklichkeit erlauben würden, liegen jedoch bisher nicht vor. - Wissenschaftliches Begleitprogramm: Neben der Untersuchung der symptomatischen Wirksamkeit der Kunsttherapie soll die Studie dazu beitragen, neue Erkenntnisse über Wirkfaktoren der Kunsttherapie, wie sie z.B. in der Patient-Therapeut-Interaktion zu erwarten sind, zu erbringen. Um diese Prozessforschung betreiben zu können, planen wir jede Kunsttherapieeinheit auf Video mitzuschneiden. Videoaufnahmen sollen neben der Sicherung der Therapieadhärenz der Therapeuten zur Gewinnung von objektiven und beobachtbaren Informationen über die Interaktionen und Veränderungen zwischen Patient und Therapeut und Gruppe dienen. Diese Beobachtungen werden von nicht am Therapieprozess beteiligten Personen ausgewertet und in Beziehung zu den Beobachtungen des Therapeuten und seinen Therapieprotokollen gesetzt. Vergleiche sollen zu gesicherten Einschätzungen von Verhalten und Veränderungen der Patienten führen. |
| **Prüfmedikation / Behandlungsstrategie** | Die kunsttherapeutische Intervention findet zweimal wöchentlich in Gruppen mit bis zu fünf Patienten statt. Eine Einheit dauert jeweils 90 Minuten. Insgesamt werden zwölf Einheiten Kunsttherapie in sechs Wochen angeboten. Die letzten  Einheiten der Intervention können auch nach der Entlassung  aus der Klinik als poststationäre Therapiegruppe besucht  werden. |
| **Vergleichstherapie** | Standardtherapie (Treatment as usual) |
| **Studiendesign** | Es handelt sich um eine prospektive, randomisierte  kontrollierte Pilotstudie.Alle Patienten erhalten die indizierte psychopharmakologische und ärztliche Behandlung und können an den Therapien der Station uneingeschränkt teilnehmen. Lediglich der Umgang mit Kunst darf nicht gefördert werden (Museumsbesuche, kreatives Arbeiten mit Material). |
| **Zeitplan** | - Beginn der Rekrutierung: Januar 2011 - Erwartetes Ende der Rekrutierung: Juni 2011 - Erwartetes Ende der Studie: August 2011 |
| **Gesamtzahl Patienten** | Es ist geplant, 15 Patienten pro Studienarm einzuschließen. |
| **Einschlusskriterien** | - Diagnose einer Schizophrenie gem. DSM-IV - Alter 18-64 Jahre - Ausreichend deutsche Sprachkenntnisse - Schriftliche Einwilligung (DvH, ICH-GCP) |
| **Ausschlusskriterien** | - Organische Hirnerkrankung - Sonstige psychische Störung gemäß DSM-IV- Achse I - Antisoziale Persönlichkeitsstörung gemäß DSM-IV - Relevante schwere somatische Erkrankung - Relevanter Konsum oder von Alkohol und illegalen Drogen (Ausschluss durch Drogenscreening im Urin) - Unfähigkeit, Inhalt und Bedeutung der Studie zu verstehen und informierte Einwilligung schriftlich zu geben. - Aktuelle Fremdgefährdung, Suizidalität oder andere Selbstgefährdung. - Unterbringung gem. PsychKG - Mangelnde Eignung für gruppenpsychotherapeutische Verfahren: 1. stark ausgeprägte Antriebsstörung, Feindseeligkeit oder Aggressivität, 2. schwere Impulskontrollstörung, 3. schwerste paranoide Symptomatik. |
| **Dokumentationszeitpunkte** | Screeninguntersuchung (Visite -1)/ Randomisierung/ Baseline-Untersuchung (Visite 1, Woche 1)/ Untersuchung nach Interventionsende (Visite 2, Woche 6)/ Untersuchung zum Follow-up (Visite 3, Woche 12) |
| **Zielgrößen** | Primäre Zielparameter:   - Reduktion von psychotischen Positiv- und Negativ-Symptomen in SANS und SAPS-Score, - Depressivität (Calgary Depression Scale), - Psychosoziale Funktion (global assessment of functioning, GAF)   Sekundäre Zielparameter:   - Patientenzufriedenheit (Fragebogen für Zufriedenheit mit der stationären Behandlung (ZUF-8) - Lebensqualität (Modular System for Quality of Life) - Selbstwirksamkeitserwartung (Fragebogen zu Kompetenz und Kontrollüberzeugungen) - Mentalisierungsfunktionen (ToM: Reading the Mind in the Eyes Test); Gewahrsein von Emotionen in sozialen Situationen: Levels of Emotional Awareness Scale (LEAS)) |
| **Sicherheit** | Abfrage und Dokumentation unerwünschter Ereignisse zu jeder Visite. Im stationären Verlauf kontinuierliche Beurteilung und Dokumentation der Symptomschwere und etwaiger unerwünschter Ereignisse. Die Teilnehmer werden weiterhin aufgefordert, sich bei Auftreten von unerwünschten Ereignissen zwischen den Visiten umgehend zu melden. |
| **Abbruchkriterien** | Im Einzelfall:   - Suizidalität - Exacerbation der psychotischen Störung - Fremdgefährdung - Neuauftreten von Ausschlusskriterien - Unterbringungsbedürftigkeit nach dem PsychKG.   Insgesamt:  Sollten mehrere Patienten durch die Behandlung destabilisiert werden, und Suizide, Exacerbationen, Gewalt oder Unterbringungen nach dem PsychKG vermehrt auftreten, so kann die Studienleitung über den Abbruch der Studien entscheiden. |
| **Statistische Auswertung** | Die statistische Analyse in Bezug auf die Outcome-  Parameter soll mit Hilfe von T-Tests, ANCOVA und MANCOVA mit Meßwiederholung als Intention-to-treat-Analyse vorgenommen werden, wobei ausscheidende Studienprobanden in die Endanalyse einbezogen werden und die Gründe für das Ausscheiden angegeben werden. |
| **Präklinische Untersuchungen** | Ohne Relevanz |
| **Mögliche Risiken, Kontraindikationen, Maßnahmen, die bei eventuellen Zwischenfällen zu ergreifen sind** | Mögliche Risiken:   - Durch die Bearbeitung von Ängsten, inneren Konflikten oder paranoid belegten Themen während der therapeutischen Intervention könnte es zu einer temporären Destabilisierung des Patienten mit steigender Dynamik von Wahn, Halluzinationen und formalen Denkstörungen oder Depressivität kommen. - In einzelnen Fällen könnte die Gefahr von Fehlverhalten mit Gefährdung des Patienten selbst oder Dritter ebenfalls zunehmen. Mögliche Nebenwirkungen/ Komplikationen wären dann: Suizidalität, Suizidversuche, Suizid und Aggressivität.   Kontraindikationen: siehe Ausschlusskriterien (auch Neuauftreten von Ausschlusskriterien)  Maßnahmen, die bei eventuellen Zwischenfällen zu  ergreifen sind:   - Deeskalierende und stützende Intervention durch den Kunsttherapeuten. In der Regel sollte die Therapieeinheit nach einem Krisengespräch und eventuell einer kurzen Pause mit allen Teilnehmern zu Ende geführt werden. Bei schweren Erregungszuständen muss die Therapieeinheit für den betroffenen Patienten abgebrochen werden. In diesem Fall sowie bei Verdacht auf Suizidalität oder Eigen- und Fremdgefährdung muss der behandelnde Arzt sowie der Studienarzt informiert werden. Geeignete Schutzmaßnahmen werden durch den Arzt eingeleitet. |
| Risiko-Nutzen-Abwägung | Die Kunsttherapie birgt aller Erfahrung nach für die Teilnehmer  nur geringe Risiken, und diese können im stationären  Behandlungsrahmen minimiert werden. Sollte es zu Steigerung  ängstlicher Erregung, Anspannung oder Feindseligkeit und Aggressivität kommen, so wäre der Therapeut zu einer geeigneten Deeskalation in der Lage und könnte jederzeit umgehend auf ärztliche Hilfe zurückgreifen, wenn dies notwendig sein sollte. Bei geringer Gruppengröße und  erfahrenen Gruppenleitern sollte in den meisten Fällen ein  erfolgreiches deeskalierendes Eingreifen möglich sein. Der zu  erwartende Nutzen der Intervention überwiegt bei weitem die  Risiken. Ärztliche Hilfe und Hilfe von Krankenpflegekräften steht auf der Station ständig zur Verfügung. |

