## Trial Design Overview

The study is planned and performed as a monocentric, randomised controlled pilot study with two parallel groups. The intervention group will be administered 12 sessions of psychodynamic art therapy (twice weekly over 6 weeks, 90 minutes per session), in groups of up to 5 patients, led by a trained art therapist experienced in the treatment of psychoses. The intervention will be aided and each sessions will be video-taped by a trained auxiliary person.

Patients randomisd to the control group will receive treatment as usual (TAU), including all indicated therapy options provided by the study centre. Allocation is open for patients, the art therapist, supervisors and all persons directly involved in the practical execution of the trial.

Psychopathological ratings (SAPS, SANS, CDSS, GAF) are performed by clinicians responsible for the study who are blind to randomisation status. In this pilot study, at least 15 patients will be included into each arm. The total individual trial duration is 12 weeks.

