## Procedures in case of emergency

In case of an exacerbation of symptoms or severe adverse reactions associated with the study intervention, emergency measures can be taken at any time by the treating psychiatrist, the psychiatrist in charge and senior physicians of the hospital. Symptoms associated with the study intervention may comprise suicidal intention, self-harm, endangerment of others, material damage, increase in psychotic symptoms like desorganisation, delusions, hallucinations, psychomotor agitation or stupor, affective tension, anxiety or perplexity, increase in depressive symptoms, etc.

Should critical situations arise during an art therapy session, nursing staff can immediately assist. The patient may like to finish the session and should be accompanied back to the ward. In case of severe adverse reactions, the intervention has to be discontinued immediately. The treating psychiatrist or psychiatrist in charge will be informed in any case and has to decide about further necessary measures. The treating psychiatrist will also decide about the patient's ability to continue study participation in cooperation with the principal investigator of the study. All adverse and serious adverse events are documented in the case report file and reported to the principal investigator within 24 hours.

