## Blinding Procedures

Blinding
Participants, art therapists and supervisors as well as clinical staff involved in the administration of art therapy and practical organisation of the study are aware of allocation status. Clinical ratings are performed by psychiatrists responsible for the study, but not involved in the direct treatment of the participating patients and blind to randomisation. Patients are instructed not to inform the assessor of their allocation status.

Methods of Unblinding and Discontinuation

Unblinding of the psychiatrists responsible for clinical study assessments is only allowed for safety reasons. Regular unblinding of the trial is planned at the end of the trial (last visit, last patient), after closing the database.

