## Methods of obtaining informed consent

After screening for inclusion and exclusion criteria, patients will be informed by their treating psychiatrist about the possibility of study participation at first. This should be preferably done in the first stage of the hospital stay, after completion of the admission procedure and necessary diagnostics and start of treatment. If the patient expresses approval or wishes further information, a psychiatrist responsible for the study will inform her/him about the trial. The information given covers in easily comprehensible terms the aims and organisational features of the study, nature and possible side effects of the intervention, the right to revoke previously given written consent and to withdraw from the study at any time without disadvantage and without having to give an explanation, an offer of more extensive information, the allocation of patients to different treatment groups and randomisation, obligations of the patients and the care-takers, data protection and insurance issues.

Written informed consent is given after a sufficient amount of time to read the Patient Information Form handed over, to discuss the issue with relatives, caregivers and the treating physician and to ask additional questions. If the patient gives informed consent, she/he and the study physician will sign the Informed Consent Form, by which the latter confirms that inclusion criteria are met. Moreover, inclusion and exclusion criteria are confirmed by use of a structured clinical interview for DSM-IV (SCID 1 and 2) [26].

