## Assessment of causality

The determination of the likelihood that the study intervention caused the AE (causality assessment) will be provided by the investigator. The assessment of causality will be determined by the investigator and recorded on the CRF AE page and SAE form according to the investigator’s best clinical judgment. The following questions should be considered in determining the relationship between the study intervention and the AE:

- Was the study intervention administered?
- Was there another obvious cause of the AE?
- What was the temporal sequence of the onset of the AE relative to the study intervention?
- Was the AE consistent with the known pattern of response to study intervention?
- Could the subject‘s clinical state, environmental or toxic factors, or other modes of therapy administered to the subject have caused or modified the AE?
- Did the AE resolve or improve after study intervention was discontinued or reduced?
- Did the AE remain the same or worsen after study intervention was discontinued or reduced?
- If the subject was re-exposed (rechallenged), did the AE recur or worsen upon re-exposure? Did the AE not recur or improve with re-exposure? (Clinical judgment should be used for determining if rechallenge is appropriate.)

Taking into account any of the above factors, the Investigator will assess the causality of the individual AEs using one of the following:

| **unassessable:** | Due to insufficient information the causality cannot be assessed. |
| --- | --- |
| **unlikely:** | The adverse event may easily be explained with sufficient other information that there is no causality with the study intervention. |
| **possible:** | The adverse event follows a reasonable temporal sequence after administration of the intervention or a known response pattern to the suspected intervention. It could readily have been produced by the patient´s clinical state, environmental or toxic factors, or other modes of therapy administered to the patient. |
| **probable:** | The adverse event follows a reasonable temporal sequence after administration of the intervention or a known response pattern to the suspected intervention. It could not be reasonably explained by the known characteristics of the patient´s clinical state, environmental or toxic factors, or other modes of therapy administered to the patient. It disappears or decreases on cessation or reduction in dose of study intervention. |

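### Art-therapy crisis reports and adverse-event causality judgements are not kept apart from the blind ratings, so raters of all four primary endpoints can be unblinded

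*Protocol*

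**What the plan says.** **Who rates.** Protocol section 3.1 says that the SAPS, SANS, CDSS and GAF ratings "are performed by clinicians responsible for the study who are blind to randomisation status". Section 5.5 repeats this and adds that the raters do not treat the patient: "Clinical ratings are performed by psychiatrists responsible for the study, but not involved in the direct treatment of the participating patients and blind to randomisation". It permits unblinding of these raters for safety reasons only.

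**Who hears of a crisis.** The synopsis, under measures to take after incidents, covers a session broken off for severe agitation and any suspicion of suicidality or danger to self or others: "In diesem Fall sowie bei Verdacht auf Suizidalität oder Eigen- und Fremdgefährdung muss der behandelnde Arzt sowie der Studienarzt informiert werden". Section 5.4 covers the same situation but does not name the study physician: "The treating psychiatrist or psychiatrist in charge will be informed in any case". It also requires adverse events to be "reported to the principal investigator within 24 hours".

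**Who judges causality.** Section 9.5 gives the causality assessment of each adverse event to the investigator. The first question to consider is "Was the study intervention administered"; others concern timing and whether the event resolved once the intervention stopped.

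**How the roles are named.** In section 6.3, "a psychiatrist responsible for the study will inform her/him about the trial", and the study physician then signs the consent form. Section 15.1.2 gives the task of informing the patient to the study physician.

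**The concern.** The primary endpoints are clinician judgements in a trial where patients, therapist and ward staff know the allocation, so the blind of the raters is the main protection against biased scoring. The protocol states that blind, and then has a reporting rule that can send arm-revealing information to the group that rates.

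A report of a crisis in an art-therapy session can concern only a patient in that arm, and it follows deterioration. If the recipient later rates the patient, knowledge of the arm depends on both arm and outcome, and analysis cannot remove that. The rater might score more severely, because of the reported crisis, or more leniently, so the direction is not predictable.

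Section 13.1 says the trial exists to estimate effect sizes for a larger trial, so a distorted estimate would carry over into that trial's sample size.

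**Working it through.** The plan gives no figure on this point and makes no sample size calculation, so there is nothing to reproduce. The check compares the sections; the arithmetic after it is for scale only.

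**Comparison of roles**
1. Raters are study psychiatrists, blind and not treating the patient (3.1, 5.5).
2. The study psychiatrist informs the patient in 6.3, and the study physician does so in 15.1.2. The two terms therefore overlap in the protocol's own usage.
3. The study physician must be told of session crises (synopsis). With step 2, the recipient belongs to the group that rates. This link rests on the text.
4. The investigator judges causality (9.5). No section says that this person rates or does not rate. This link is inferred.
5. Adverse events are asked about at every visit (synopsis, safety row), and Table 1 in section 6.6 puts both their documentation and all four ratings at Visit 2. One clinician could easily do both.
6. Section 5.5 keeps raters out of direct treatment only. No section keeps them out of incident reports or causality assessment, or provides for a replacement rater or a record after unblinding.
7. The two routes differ. Session reports arise only in the art-therapy arm, after a crisis. Causality review covers all adverse events in either arm, including those unrelated to worsening.

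**Illustration of scale**
- Inputs from the protocol: 15 patients per arm (3.1, a minimum) and two-sided alpha 0.05 (13.2.3). Section 7.1 cites deterioration in about 10% of patients in psychotherapy generally; applying that rate to session crises here is an assumption.
- At 10%, the expected number is 15 × 0.10 = 1.5 patients, and the chance of at least one is 1 − 0.90^15 = 0.79.
- Let a share f of art-therapy patients be rated unblinded and their ratings shift by b SD, all in one direction. The spurious arm difference is d = f × b. Under no true effect, the rejection rate of a two-sample t-test follows from a noncentral t with 28 degrees of freedom and noncentrality d × √(15/2). The values of f and b are assumptions.

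| f | b (SD) | d (SD) | Rejection rate |
|---|---|---|---|
| 0.10 | 0.25 | 0.025 | 5.1% |
| 0.10 | 0.5 | 0.05 | 5.2% |
| 0.10 | 1.0 | 0.10 | 5.8% |
| 0.20 | 0.25 | 0.05 | 5.2% |
| 0.20 | 0.5 | 0.10 | 5.8% |
| 0.20 | 1.0 | 0.20 | 8.3% |
| 0.30 | 0.25 | 0.075 | 5.5% |
| 0.30 | 0.5 | 0.15 | 6.8% |
| 0.30 | 1.0 | 0.30 | 12.5% |

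The simple t-test stands in for the planned repeated-measures analysis.

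For the follow-on trial, suppose the true standardised difference were 0.40 (assumption). An error of 0.05 to 0.15 SD would multiply the planned sample size by (0.40/0.35)² = 1.31 to (0.40/0.25)² = 2.56 if the effect is understated. If it is overstated, the factor is (0.40/0.45)² = 0.79 to (0.40/0.55)² = 0.53.

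**The case against.** A reader might infer that raters are unblinded as a matter of course, and for exactly the patients who worsen. The documents do not support that, for these reasons:

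- No section says that the investigator of 9.5 is the rater. Raters are mentioned in the plural, and section 3.1 already distinguishes them from staff who know the allocation, so the tasks could be divided.
- Section 5.4 does not name the study physician as a recipient of crisis reports.
- Section 5.5 allows unblinding for safety, and suspected suicidality is a safety matter.
- The crisis triggers overlap with the individual stopping criteria in the synopsis and the withdrawal reasons in section 8.1, so some of these patients may have no later rating.
- The questions in 9.5 are factors to consider, and unassessable is an allowed answer. Causality review is also not confined to one arm or to worsening.
- At the 10% rate, the false-positive rate rises only to between 5.1% and 5.8%.

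All of this stands, and it reduces certain unblinding to possible unblinding. It does not close the gap. A possible division of tasks is not a stated one. The safety exception does not explain why the physician informed should be the one who rates that patient. The different recipients in 5.4 leave two reporting rules unreconciled. The principal investigator is no evident safeguard either, because no section says whether that person rates or is blind.

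**Conclusion.** The concern holds as a risk that the protocol leaves open. A mandatory reporting rule in the synopsis conflicts with the blind stated in sections 3.1 and 5.5, and no section keeps incident reports and causality judgements away from the clinician who rates the same patient. The link through the study physician is supported by the text; the link through the investigator of 9.5 is inferred.

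All four primary endpoints are exposed at week 6 and week 12. Baseline ratings are not, because they precede randomisation. The size and direction of any bias are unknown. Over the assumed ranges the spurious difference is 0.025 to 0.30 SD and the false-positive rate 5.1% to 12.5%. These figures assume that every affected patient is still rated and that all shifts go the same way, so they indicate scale and do not predict. The effect is probably modest, but it is cheap to prevent.

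**What to change.** Reconcile the synopsis with sections 5.4, 5.5 and 9.5 so that they agree on who receives session incident reports and who judges causality. Then state in 5.5 that, among the existing study physicians, whoever receives incident reports or completes the causality assessment for a patient does not perform that patient's week-6 and week-12 SAPS, SANS, CDSS and GAF ratings. State whether the principal investigators rate; if one does, the same rule applies. Add a CRF field for any rating made after the rater was unblinded.

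Notification of the treating physician and the emergency measures stay as they are; this point takes no position on clinical handling.

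The cost is a few sentences and one CRF field. The downside is that, with few study psychiatrists, rating and adverse-event tasks have to be divided patient by patient.
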